#### 2.5.2. Secondary Parameters

The secondary outcome measures include the following:

Body surface area (BSA): the percentage of BSA involved in psoriasis is estimated by the handprint method, in which the patient's entire palm (that is, the patient's fully outstretched palm, fingers, and thumb) represents about 1% of the total BSA [27].

Physician global assessment (PGA): the PGA is a 5-point scale that is used to reflect the overall assessment of erythema (E), infiltration (I), and desquamation (D) in psoriatic lesions [28].

Dermatology life quality index (DLQI): the DLQI is a 10-item questionnaire assessing the impact of skin disease on health-related quality of life (HRQOL). The total score ranges from 0 to 30; higher scores indicate a lower quality of life [29]. Foreign clinical studies have reported that its minimal clinically important difference (MCID) is 5 points [30]. That is, after treatment, DLQI is decreased by 5 points, which can be considered an improvement in quality of life and treatment efficacy.

Quality of life (QOL): QOL is a term used to describe a person's emotional, social, and physical health. In patients with psoriasis, QOL is similar to or worse than that of chronic diseases such as ischemic heart disease, hypertension, diabetes, and cancer [31]. The questionnaire consists of 15 questions, including five parts: daily activities, at work, personal relationships, leisure activities, and treatment. The answer to each question gives a score from 0 to 3. The choice of each question is “very many” (3 points), “a lot” (2 points), “a little” (1 point), and “no answer at all” (0 points) [32].

Visual Analogue Scale (VAS): VAS is an often-used tool to measure subjective phenomena, which has shown good reliability and validity in terms of assessment of pain. In the clinical study of psoriasis, it can be used as a tool to measure the degree of pruritus from 0 to 100 mm (with 0 being no pruritis and 100 being maximum pruritis) [33].

CM syndrome scoring scale (CMSSS): the CMSSS is used to assess changes in blood-hot syndrome-related symptoms during treatment [2].

The BSA, PGA, and VAS will be assessed every two weeks during the treatment period and every four weeks in the follow-up period. The DLQI, QOL, and CMSSS will be assessed by the patients every two weeks during the treatment period. In the follow-up period, the DLQI will only be assessed in the last week (week 16). Laboratory reports will also be monitored until the last visit (Table 2).

#### 2.5.3. Sample Size

The sample size for this study was calculated based on the expected value of the efficacy according to the clinical trial results and data analysis of recently published articles [34, 35]. The PASI-50 reached for experimental group and control group was 55.66% and 35.3%, respectively. The significance level (alpha) was set at 0.05, and the statistical power was 80%. Based on our calculation using the PASW statistical software (V.18.0), a sample size of 89 patients was required for experimental group and control group. Given a 10% loss to follow-up, we expect to require 98 participants in each group. As a result, this trial will require at least 196 participants in its current setup.

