### 2.5. Outcome Measures

#### 2.5.1. Primary Outcome

The primary outcome is the reduction in the Psoriasis Area Severity Index (PASI) score, which will be calculated as follows: PASI reduction = (PASI at baseline)–(PASI at week 8 of the treatment period).

The PASI score of the patients will be assessed every 2 weeks during the treatment period and every 4 weeks during the follow-up period. The main result of the RCT will be the percentage of patients whose PASI score decreased by more than 75% compared with the baseline at 8 weeks [2].

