#### 2.5.11. Statistical Analysis

The data analysis will be performed using SAS software (version 9.2). We will describe the data by using frequency counts and proportions (prevalence) for qualitative variables and means. Standard deviation (SD) will be used for normally distributed quantitative variables, while median and interquartile range (Q1 and Q3) will be used for nonnormally distributed quantitative variables. We will apply the chi-square test to examine the differences between the experimental and control groups for qualitative variables, the *t*-test to examine the differences between two groups for normally distributed quantitative variables (the homogeneity of variance will be tested between groups, and the Satterthwaite approximation will be used to correct the variance when the variance is uneven), and the Wilcoxon rank-sum test for nonnormally distributed quantitative variables. A generalized linear model will be applied for quantitative variables with repeated measures. In this study, *p* values < 0.05 (two-tailed) will be considered statistically significant.

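### The 80% power and 89 per arm were computed for PASI-50, which is not a declared outcome, so they apply neither to PASI reduction nor to PASI-75

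*Protocol article*

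**What the plan says.** Three sections of the protocol article bear on this.

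- **2.5.3 Sample Size.** The planning rates come from outside work, "according to the clinical trial results and data analysis of recently published articles". They are given as follows: "The PASI-50 reached for experimental group and control group was 55.66% and 35.3%, respectively". The section continues: "The significance level (alpha) was set at 0.05, and the statistical power was 80"%. The result is that "a sample size of 89 patients was required for experimental group and control group", and then "Given a 10% loss to follow-up, we expect to require 98 participants in each group", for a total of 196.
- **2.5.1 Primary Outcome.** The primary outcome is PASI reduction, defined as the baseline score minus the week 8 score, so it is an absolute change. The same section then states: "The main result of the RCT will be the percentage of patients whose PASI score decreased by more than 75"% from baseline at 8 weeks.
- **2.5.11 Statistical Analysis.** Tests are two-sided: "values < 0.05 (two-tailed) will be considered statistically significant".

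PASI-50 is mentioned only in section 2.5.3. It is absent from the abstract, the primary and secondary outcomes, the analysis section and Table 2. Nothing links the PASI-50 rates to PASI-75 or to mean PASI reduction.

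**The concern.** A power figure holds for one endpoint under one set of assumptions. Here the only power figure is attached to an endpoint that the trial does not declare, while two other quantities are put forward as primary outcome and main result. This is not a detail that a separate analysis plan could supply: the article states both its outcomes and its sample-size basis, and they disagree.

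What is at stake is how the result will be read. If the PASI-75 comparison is not significant, readers will take 196 patients and 80% power as a sign that a worthwhile effect would have been found. The document gives no basis for that inference, for PASI-75 or for mean PASI reduction.

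**Working it through.** **Step 1: reproduce the plan's figure.** Inputs from section 2.5.3: p1 = 0.5566, p2 = 0.353, alpha 0.05, power 80%. Two-sided testing is taken from section 2.5.11, because section 2.5.3 does not state it.

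Unpooled normal approximation:

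n = (1.960 + 0.842)² × [p1(1−p1) + p2(1−p2)] / (p1−p2)²
= 7.849 × (0.2468 + 0.2284) / 0.2036²
= 7.849 × 0.4752 / 0.04145 = 89.97 per arm.

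This matches the stated 89 if truncated. The pooled-null formula gives 93, and its power at 89 per arm is 78.4%. For dropout, 89 × 1.10 = 97.9, which gives 98. The arithmetic is therefore consistent, and it is tied to the PASI-50 rates.

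**Step 2: what the document supplies for the declared endpoints.**

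| Endpoint | Status in section 2.5.1 | Input needed for power | Given? |
|---|---|---|---|
| PASI reduction (absolute) | primary outcome | mean difference and SD | no |
| PASI-75 | main result | response rate in each arm | no |
| PASI-50 | not declared | response rate in each arm | yes |

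One constraint does follow. Anyone whose PASI falls by more than 75% has also met the 50% threshold, so PASI-75 rates cannot exceed PASI-50 rates in either arm. This bounds the rates. It does not fix the difference between them.

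**Step 3: PASI-75 power under stated assumptions.** Evaluable per arm: 98 × 0.90 = 88.2, taken as 88. Control PASI-75 of 5% to 25% is assumed; the document gives no value. Power uses the pooled-null formula, two-sided 0.05, with p̄ the mean of the two rates:

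power = Φ{ [ |p1−p2|√n − 1.96√(2p̄(1−p̄)) ] / √[p1(1−p1) + p2(1−p2)] }

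The planning effect can be carried over in different ways:

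- **Same odds ratio:** (0.5566/0.4434) / (0.353/0.647) = 2.30.
- **Same latent shift:** probit(0.5566) − probit(0.353) = 0.142 + 0.377 = 0.52 SD.
- **Same difference:** 55.66 − 35.3 = 20.36 points.

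| Control PASI-75 | Odds ratio 2.30: treated rate, power | 0.52 SD shift: treated rate, power | 20.36 points: treated rate, power | Treated rate for 80% power |
|---|---|---|---|---|
| 5% | 10.8%, 30% | 13.0%, 46% | 25.4%, 97% | 18.5% |
| 10% | 20.4%, 48% | 22.3%, 60% | 30.4%, 93% | 26% |
| 15% | 28.9%, 61% | 30.3%, 68% | 35.4%, 88% | 33% |
| 20% | 36.5%, 68–69% | 37.4%, 73% | 40.4%, 84% | 39% |
| 25% | 43.4%, 73% | 43.8%, 75% | 45.4%, 81% | 45% |

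A constant risk ratio (0.5566/0.353 = 1.58) would give less than any of these: 12%, 21%, 31%, 42% and 54%. By the same formula the PASI-50 planning rates give 78% at 88 per arm, so the spread in the table comes from the change of endpoint and the assumed effect, not from the choice of formula.

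**Step 4: PASI reduction.** With no SD, only a standardised figure is possible. The standardised difference detectable with 80% power is (1.960 + 0.842) × √(2/88) = 0.42 SD. Whether the expected effect reaches that cannot be told from the document.

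**The case against.** The strongest objection is to any claim that the trial is underpowered. A reader might infer from the stricter threshold that power for PASI-75 is well below 80%. The documents do not support this. They give no PASI-75 rate for either arm, and the low figures depend on carrying over an odds ratio, a risk ratio or a latent shift. If the planned 20.36-point difference is kept, power is above 80% across the whole control range shown. That assumption may not be the likeliest, but nothing in the document excludes it. This objection stands in full.

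The opposite inference is also tempting: that a 0.52 SD shift makes the continuous primary outcome amply powered. That does not hold either. The shift comes from a threshold on percentage change, whereas section 2.5.1 defines an absolute reduction, whose SD also depends on the unstated spread of baseline PASI.

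It can also be said that PASI-50 could be derived from the PASI scores collected at every visit, that the calculation is sound for its own inputs, and that recruitment had already begun. All of this is true. None of it makes the stated 80% apply to an endpoint that section 2.5.1 declares.

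**Conclusion.** The point holds as a mismatch of endpoints, not as an arithmetic error or a demonstrated lack of power. The stated 80% and 89 per arm are reproducible for PASI-50 and apply to neither PASI reduction nor PASI-75. Power for the declared endpoints is unstated and cannot be derived from the document.

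The possible size for PASI-75 runs from about 30% to 97% over the three assumptions tabulated, and lower still under a constant risk ratio. All of these rest on an assumed control rate of 5% to 25%, 88 evaluable per arm and a two-sided 0.05 test. The mismatch itself depends on none of those assumptions. It should be corrected because it removes the only power justification that the trial offers.

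**What to change.** 1. In section 2.5.1, name one primary endpoint. The remaining changes depend on that choice.
2. Restate section 2.5.3 for that endpoint at the planned 98 per arm, about 88 evaluable:
   - for PASI-75, give assumed rates in both arms with their source and the resulting power, or give the detectable difference (for example, 26% vs 10% or 33% vs 15% for 80% power);
   - for PASI reduction, give the assumed mean difference and SD with their source and the resulting power.
3. Remove the statement that the PASI-50 calculation gives the trial 80% power. The PASI-50 figures may stay as a record of how 196 was reached, if labelled as such.

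The cost is one rewritten paragraph and one clarified sentence. No extra patients, visits or data are asked for. The only downside is that the stated power may become less favourable.

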## Abstract

*Introduction*. The etiology and pathogenesis of psoriasis are complex. Blood-heat syndrome is the core pathogenesis of psoriasis. Based on theories of Chinese medicine (CM), heat-clearing and blood-cooling (HCBC) are the primary treatment. Very few studies have investigated the pharmacological mechanism of the CM HCBC method for treating psoriasis. This multicenter randomized controlled trial will focus on treating psoriasis blood-heat syndrome with the HCBC method using Jueyin granules (JYKL). This will be an objective and standardized evaluation of the efficacy, safety, and reproducibility of the HCBC method to obtain objective evidence meeting international standards that aim to establish a clinical standard suitable for the popular application of CM for treating psoriasis. *Methods and Analysis*. A five-center randomized double-blind placebo-controlled clinical design will be used in this study. At least 196 participants will be randomly assigned to receive either JYKL or placebo treatment approximately 30 minutes after meals in the morning and evening (one sachet per time, twice daily for 8 consecutive weeks). The study duration will be 17 weeks, including 1 week of screening, 8 weeks of intervention, and 8 weeks of follow-up. The patients will be evaluated every 2 weeks, and the measures will be compared with baseline values. The primary outcome measure will be the psoriasis lesion area severity index. We will also observe the recurrence rate, body surface area, physician global assessment, dermatology life quality index, quality of life index, visual analogue scale score, CM symptom score, combined drug use, and adverse events. This trial is registered with NCT03961230.

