## 2. Methods and Analysis

### 2.1. Study Design

This will be a multicenter randomized double-blind placebo-controlled clinical trial. It will aim to objectively standardize the evaluation of the clinical efficacy, safety, and recurrence of blood-heat syndrome of psoriasis vulgaris treated with HCBC in CM. The results will be helpful for establishing the clinical standard of traditional CM in the treatment of psoriasis. The trial has been registered at NCT03961230. The start and end of recruitment was planned for January 2019 and December 2021, respectively.

Prior to the commencement of the study, the investigators and researchers require uniform training to ensure that the medical staff involved in the study are fully aware of all aspects of the trial. This study will be performed in five centers in China: Yueyang Integrated Traditional Chinese and Western Medicine Hospital, Beijing Traditional Chinese Medicine Hospital, First Affiliated Hospital of Anhui University of Traditional Chinese Medicine, Affiliated Hospital of Gansu University of Traditional Chinese Medicine, and Guangxi Zhuang Autonomous Region Institute of Dermatology Prevention and Control. Competitive enrollment will be applied in all research centers to achieve the goal of 196 total participants. Each participant can be enrolled only once.

Five phases will be included in the study: screening/registration, allocation, treatment/intervention, end of the intervention, and follow-up. During the initial screening, participants will be recruited through dermatology clinics, where they will undergo a physical examination and eligibility assessment. According to the assessment results, a run-in period of up to one week will be required. All patients who are diagnosed with psoriasis with blood-heat syndrome will undergo laboratory blood testing, including a complete blood cell count, liver function test, renal function test, and a pregnancy test before study inclusion. Additionally, routine urine tests, vital sign monitoring, and physical examinations will be performed (Figure 1). Patients who are willing to join the clinical trial will receive study information and consent forms. The consent forms must be signed before a patient will be included in this study.

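### At the planned 10% loss, 98 patients per group leaves an expected 88.2, just under the 89 that the sample-size section requires

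*Protocol article*

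**What the plan says.** Section 2.5.3 (Sample Size) of the protocol article builds the recruitment target in three steps.

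- **Planning inputs.** "The PASI-50 reached for experimental group and control group was 55.66% and 35.3%, respectively". On error rates: "The significance level (alpha) was set at 0.05, and the statistical power was 80" per cent.
- **Requirement before losses.** "a sample size of 89 patients was required for experimental group and control group". The next step uses this as 89 in each group.
- **Allowance and total.** "Given a 10% loss to follow-up, we expect to require 98 participants in each group", and then "this trial will require at least 196 participants in its current setup".

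The article does not say how the 10% was applied or how the result was rounded. The total appears twice more, in the abstract ("At least 196 participants will be randomly assigned") and in section 2.1, where enrolment across the five centres is competitive ("to achieve the goal of 196 total participants").

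**The concern.** An allowance for loss to follow-up is meant to leave the required number of patients once the loss has occurred. The three figures in section 2.5.3 (89, 10% and 98) do not achieve that. If 10% of 98 patients are lost, slightly fewer than 89 are expected to remain.

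The figure carries weight because 196 is the recruitment target wherever the article gives one. A trial that stops at 196 has done what the protocol asks. If it then loses patients at exactly the planned rate, it can expect to finish a little below its own requirement. What is at stake is a sample-size statement that any reader can recompute and find inconsistent. The threat to the trial's power is slight.

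**Working it through.** **Inputs**, all from section 2.5.3 unless noted: response rates 0.5566 and 0.353; alpha 0.05, two-sided according to section 2.5.11 ("values < 0.05 (two-tailed) will be considered statistically significant"); power 80%; 89 required per group; loss 10%; 98 per group; total 196.

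**1. Where the 89 comes from (background only).** The two-proportion normal approximation with unpooled variance gives

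n = (1.96 + 0.8416)² × [0.5566 × 0.4434 + 0.353 × 0.647] / (0.5566 − 0.353)² = 7.849 × 0.47519 / 0.2036² = 89.97.

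This is 90 when rounded up and 89 when truncated. Other common versions lie further away: 93 with pooled variance, 103 with a continuity correction, 92.5 with the arcsine transformation, and 73 or 83 one-sided. The steps below take 89 as given and do not depend on which formula produced it.

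**2. Reproducing the 98.** Two routes lead to it:

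- 89 × 1.1 = 97.9, rounded up to 98;
- 89 / 0.9 = 98.89, rounded down to 98.

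The article does not let the reader tell them apart.

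**3. Does 98 keep 89?**

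| Enrolled per group | Expected after 10% loss, per group | Expected in total | Required per group / in total |
|---|---|---|---|
| 98 | 98 × 0.9 = 88.2 | 176.4 | 89 / 178 |
| 99 | 99 × 0.9 = 89.1 | 178.2 | 89 / 178 |

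The shortfall at 98 is 0.8 of an expected patient per group. The smallest whole number that meets the requirement in expectation is 99 per group, 198 in total.

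**4. What loss 98 can absorb.** Keeping 89 of 98 allows 9 losses, and 9 / 98 = 9.2%.

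**5. Chance variation.** Assume that each patient is lost independently with probability 0.10. An arm of 98 then ends with 88 or fewer patients with probability 0.52, and an arm of 99 with probability 0.40.

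**6. Effect on power.** At the planning rates:

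| Patients per group | Unpooled formula | Pooled formula |
|---|---|---|
| 88 | 79.1% | 77.9% |
| 89 | 79.6% | 78.4% |

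The difference is less than half a percentage point under either formula.

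**The case against.** The strongest case on the other side is that this is rounding and not worth a correction.

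- **The cause is not documented.** A reader might infer that the authors applied the wrong operation, multiplying by 1.1 where they should have divided by 0.9. The article does not support that as a fact. It prints no formula, and the correct division truncated to a whole number gives the same 98. Truncation is plausible, because the 89 itself matches the unpooled formula only when 89.97 is cut down. This stands, so the point is confined to the result. The result is the same by either route, since a required minimum should be rounded up.
- **The gap is tiny.** It is one patient per group, about 1% of the sample, against a loss rate that is itself a round planning guess. This stands and sets the low weight of the point, but it does not make the three figures agree.
- **The target is worded as a minimum.** Section 2.5.3 and the abstract both say at least 196, so enrolling 198 would comply. This helps only in part. The stated minimum is the figure that is too low, and section 2.1 treats 196 as the goal.
- **The correction guarantees nothing.** An arm of 98 still has about a 48% chance of keeping 89 or more, and an arm of 99 still falls short about 40% of the time. This is right. The inconsistency concerns expected numbers, and it would be wrong to say that the trial will end below its requirement.
- **A larger question is left aside.** The calculation uses PASI-50 response, while section 2.5.1 describes a score reduction and a response above 75%. Redoing the calculation for those endpoints could replace 89, 98 and 99 together. That is a separate matter. For as long as 89 stands, the allowance built on it should be right.

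**Conclusion.** The point holds as a small inconsistency. With 89 required per group and 10% loss, the stated 98 leaves an expected 88.2 per group (176.4 in total) against 89 (178), and 99 per group (198 in total) is needed to keep 89 in expectation.

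The conclusion rests on two readings: that 89 is the number wanted after losses, and that the 10% is a share of those enrolled. Both are the natural sense of section 2.5.3. The conclusion does not rest on the response rates, the sidedness of the test or the formula behind the 89.

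A reader might take this to mean that the trial is underpowered by the slip. The figures do not support that, since the loss is under half a percentage point of power at the planning rates.

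**What to change.** Either of two changes resolves it.

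1. **Keep 196 and restate section 2.5.3**, for example: *98 per group retains 89 evaluable patients if loss to follow-up does not exceed 9.2%; at 10% loss about 88 per group are expected.* This costs one sentence and leaves recruitment unchanged, which suits a trial that is already recruiting according to section 2.5.9.
2. **Correct the figures** to 99 per group and 198 in total in section 2.5.3, section 2.1 and the abstract. This costs two more participants, which the at-least wording already permits.

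Under either option, adding the formula and the rounding rule used for the allowance would let readers reproduce the figure.

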#### 2.5.4. Randomization, Allocation, and Blinding

This study will use central district stratification and block randomization. Random sequences will be generated by statistician researchers (implemented by the data Management Center of Jiangsu Famous Medical Technology Co. Ltd.). Eligible patients will be randomly assigned, in a 1 : 1 ratio, to one of the two groups (JYKL group or control group), aiming to balance baseline characteristics between the groups.

Throughout the study, participants, subjects, and study monitors will be blinded. Research drug random coding will be the only information linked to the group allocations. The random code will be maintained by Jiangsu Famous Medical Technology Data Management Center to ensure concealment. For the purpose of the statistical analysis, the JYKL intervention will be considered the exposure. If a serious adverse event occurs and the patient needs to be rescued, making it is necessary to know the drug used by the patient, the person in charge of each center shall decide to open the blindness and open the corresponding emergency letter. As soon as the corresponding numbered emergency letter is opened, the case will not be included in the study.

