#### 2.5.5. Safety Evaluation

Vital signs, adverse events, and severe adverse events will be evaluated before treatment at the following points: week 0, week 2, week 4, week 6, week 8, and during week 16 follow-up period. We will evaluate the blood routine, blood biochemistry, routine urine, and physical examination during the screening period, the 8^th^ week of treatment, and the follow-up period (16^th^ week). We will screen for pregnancy during the initial participant screening (Table 2).

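### Opening the emergency code excludes a randomised patient from the study: read as written, code-broken cases leave the efficacy comparison, and their serious events could leave the safety results

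*Protocol article*

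**What the plan says.** Section 2.5.4 (Randomization, Allocation, and Blinding) describes one situation in which the code is opened during the trial: "If a serious adverse event occurs and the patient needs to be rescued", so that the drug has to be known. The decision is local: "the person in charge of each center shall decide to open the blindness and open the corresponding emergency letter". The consequence follows at once: "As soon as the corresponding numbered emergency letter is opened, the case will not be included in the study".

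Section 2.5.5 (Safety Evaluation) says "Vital signs, adverse events, and severe adverse events will be evaluated" at weeks 0, 2, 4, 6, 8 and 16. It does not say how code-broken patients are treated.

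Section 2.5.11 (Statistical Analysis) names the tests but nothing that limits or overrides the exclusion. Section 2.5.10 leaves the detailed analysis plan to a separate document.

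**The concern.** The code break comes after allocation, and its trigger is a serious adverse event that the study drug may have caused. Excluding patients on that basis means the groups compared are no longer those that randomisation formed. If one arm has more code breaks, and those patients tend not to respond, that arm loses failures from its denominator and its response rate rises. Because each centre decides whether to open the letter, inclusion in the analysis would also depend on local judgement.

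The safety side may matter more. Safety is a stated aim of the trial (section 2.1). If the whole case is dropped, the event that led to the code break goes with it, and that event was serious enough to need rescue with knowledge of the drug.

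This is a rule that the article states, not a detail left to the analysis plan. A plan that follows it carries the problem forward, and a plan that keeps these patients contradicts it.

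**Working it through.** **1. What the rule covers.** Setting the sentences of section 2.5.4 side by side, exclusion needs four things: a serious adverse event, a need for rescue, a need to know the drug, and a centre's decision to open the letter. A serious event without a code break stays in. The exclusion is not limited to efficacy, to a per-protocol set or to further blinded dosing.

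**2. The plan's own figure.** Section 2.5.3 states: "The PASI-50 reached for experimental group and control group was 55.66% and 35.3%, respectively". It uses alpha 0.05 and 80% power, and section 2.5.11 makes tests two-tailed. With the unpooled normal formula:

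n = (1.960 + 0.842)² × [0.5566 × 0.4434 + 0.353 × 0.647] / (0.5566 − 0.353)² = 7.849 × 0.4752 / 0.04145 ≈ 89.97, so 90 per arm against the stated 89.

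The stated 98 is 89 × 1.10 = 97.9, rounded up. The figure reproduces to within one patient. The point does not depend on it; it only supplies the denominators below.

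**3. Effect on the response rate (assumed counts).** The article gives no code-break rate and no PASI-75 planning rate, so the PASI-50 planning rates are used: 98 × 0.5566 ≈ 55 JYKL responders and 98 × 0.353 ≈ 35 placebo responders. Assume that k code-broken patients in one arm, all non-responders, are dropped. If kept, the rates are 55/98 = 56.1% and 35/98 = 35.7%. If dropped:

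| k | JYKL rate, 55/(98 − k) | Shift (points) | Placebo rate, 35/(98 − k) | Shift (points) |
|---|---|---|---|---|
| 0 | 56.1% | 0 | 35.7% | 0 |
| 1 | 56.7% | +0.6 | 36.1% | +0.4 |
| 2 | 57.3% | +1.2 | 36.5% | +0.7 |
| 5 | 59.1% | +3.0 | 37.6% | +1.9 |

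Code breaks on JYKL widen the apparent difference; code breaks on placebo narrow it.

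**4. Effect on false positives.** In a simulation with no true difference (35.3% response in both arms, 98 per arm, 400,000 runs), k non-responders were dropped from JYKL only. The chance of a significant result favouring JYKL was 2.4% for k = 0, 3.2% for k = 2, 4.4% for k = 5 and 8.0% for k = 10. Ten is an extreme count, shown only to mark the end of the range.

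**5. Effect on safety.** If the cases are removed entirely, 1 code-broken event among 98 (1.0%) is reported as 0 of 97, 2 of 98 (2.0%) as 0 of 96, and 5 of 98 (5.1%) as 0 of 93.

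**The case against.** The strongest reply is that the sentence may mean only that the patient leaves blinded participation. Section 2.5.4 does not mention the safety analysis. Section 2.5.5 says that adverse events will be evaluated and makes no exception for unblinded patients. The article is condensed and the analysis plan is not shown, so the absence of a named safety set does not show that these events go unreported. This stands in part: loss of the safety data is a consequence of the literal wording, not a stated intention. But nothing in the article confirms the milder reading, and the sentence refers to the case and the study without qualification.

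The second reply is size. Treatment lasts 8 weeks, lesions must cover less than 10% of body surface (section 2.2.1), and serious systemic disease is excluded (section 2.2.2). Code breaks may well be few or none. This stands for efficacy: with 0 to 2 cases the shift is at most about 1.2 points. The illustration also assumes that every dropped patient is a non-responder and that only one arm is affected.

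A reader might infer that the trial's worst outcomes in general disappear from the results, or that the rule favours JYKL. The documents support neither. Only code-broken cases are covered, and the direction of any bias depends on which arm has them.

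**Conclusion.** The rule is wrong as written and should be replaced. Taken literally, it excludes randomised patients for a post-randomisation event that treatment may cause, and nothing shown limits it. On the assumed counts, the efficacy bias is small: 0 to 1.2 points in the JYKL rate for 0 to 2 cases and 3.0 points for 5, with the sign reversed in the treatment difference if the cases are on placebo. The case for the change rests more on safety. On the literal reading, every serious event that led to unblinding would be lost, whatever the count. That consequence depends on the literal reading, and the code-break counts are assumptions, because the documents give none.

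**What to change.** Replace the last sentence of section 2.5.4 with text to this effect, and carry it into the analysis plan:

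> Patients whose code is opened stay in the group to which they were randomised for the efficacy analysis, and all who took study drug stay in the safety set. Code breaks are reported by arm with date and reason. For PASI-75 at week 8, those without a valid week-8 PASI count as non-responders; for the PASI reduction, they are handled by the same missing-data method as other patients. Exclusion of code-broken patients is a sensitivity or per-protocol analysis only.

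Both measures are named because section 2.5.1 describes the primary outcome both as a PASI reduction and as a PASI-75 proportion.

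The change is to analysis and reporting. It does not alter emergency unblinding or clinical care. The cost is a few sentences, to be settled before the blind is opened for analysis. The drawback is that some assessments made after unblinding or rescue are kept; the sensitivity analysis shows how much they matter. Some code-broken patients may have no later PASI, because section 2.5.6 ties the 8-week follow-up to completing treatment. The replacement text covers missing week-8 values and requires no extra visits.
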